### Secondary outcome

Secondary outcomes will be analysed and reported in the same manner as the primary outcome, with the exception of time to event outcomes which will be analysed using Cox regression, and the combined analysis of function and survival which is a rank-based (non-parametric) test described in Berry *et al*.^34^ Analyses will be performed on an intention-to-treat basis, and all statistical tests will be two-tailed at 5% significance level. Further details will be provided in a full statistical analysis plan.

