### Randomisation

Participants will be allocated to one of two groups: standard treatment; standard treatment plus OptiCALS intervention (originally in a 1:1 ratio, amended during the study to a 1:2 ratio). Randomisation is via a web-based randomisation system, employing non-deterministic minimisation by including a random element into the allocation algorithm. The minimisation factors will be:

Study siteALSFRS-R trajectory since symptom onset (a measure of functional decline that can predict individuals with fast and slow disease progression)Riluzole use

The minimisation will be hosted by the Sheffield Clinical Trial Research Unit (CTRU) randomisation system, SCRAM—a remote secure server internet-based system. Access to the allocation list will only be granted to those responsible for cleaning the data and preparing unblinded data summaries during the recruitment and follow-up. For all other members of the trial team, the allocations will be concealed until recruitment and data collection are complete.

A CTRU statistician who is not otherwise associated with the trial will generate the allocation sequence. Named persons on the delegation log, who are trained in research procedures, will allocate participants by logging into SCRAM and entering basic demographic information.

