### Secondary outcomes

#### Combined Assessment of Function and Survival (CAFS)

This analysis ranks clinical outcomes on the basis of survival and change in ALSFRS-R scores.^34^ Each patient’s outcome is compared with every other patient’s outcome, assigned a score, and the summed scores are ranked. The mean rank score for each treatment group can then be calculated.

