## Data analysis

### Primary outcome

The primary outcome ALSFRS-R will be analysed longitudinally using a multilevel linear mixed effect model estimated by restricted maximum likelihood. The fixed effect covariates will be time, treatment and their interaction together with variables used in the minimisation process. The recruitment centre will be incorporated as a random intercept in which participants are nested within their centre. If this model fails to converge, the centre effect will be removed and the simpler model will be fitted. The area between the two ALSFRS-R curves will be derived using a linear combination of the coefficients for treatment and the interaction of treatment with time and will be presented alongside its 95% CI and p value. The difference in ALSFRS-R will also be quantified separately at each timepoint.

The primary analysis will be intention-to-treat and will include all patients for whom data are collected or who have died; an ALSFRS-R functionality score will be assigned for all timepoints scheduled after the date of death. Sensitivity analyses will be performed to assess the robustness of the findings to distributional assumptions, baseline characteristics and imbalance, missing data and non-adherence.^46^

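### The CAFS rank test is taken out of the adjusted analysis and described with no account of the minimisation factors; run that way it is valid but conservative and gives up some power

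*Protocol article*

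**What the plan says.** All references are to the protocol article.

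- **Randomisation.** Allocation is by minimisation with a random element on three factors: study site, ALSFRS-R trajectory since symptom onset, and riluzole use. Trajectory is described as "a measure of functional decline that can predict individuals with fast and slow disease progression".
- **Data analysis, Primary outcome.** The mixed model has time, treatment and their interaction "together with variables used in the minimisation process", with centre as a random intercept.
- **Data analysis, Secondary outcome.** The default is stated first: "Secondary outcomes will be analysed and reported in the same manner as the primary outcome, with the exception of time to event outcomes". Time-to-event outcomes go to Cox regression. The other exception is "the combined analysis of function and survival which is a rank-based (non-parametric) test", for which a published method is cited. The section closes: "Further details will be provided in a full statistical analysis plan".
- **Combined Assessment of Function and Survival (CAFS).** Patients are compared pairwise, and the scores are summed and ranked. "The mean rank score for each treatment group can then be calculated". No stratum or covariate appears.

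**The concern.** Minimisation makes the arms alike on trajectory. Variation between fast and slow progressors then contributes almost nothing to the difference between arms. A test that leaves trajectory out still counts that variation in its standard error. The standard error is too large, the test rejects less often than 5% under the null, and power falls.

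This applies to CAFS in particular because CAFS ranks survival and change in ALSFRS-R, and the article says trajectory predicts how fast patients progress. The primary analysis uses this information. For CAFS, the outcome that combines function and death, the article describes an analysis that does not.

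**Working it through.** **Inputs from the Sample size section.** Baseline ALSFRS-R mean 37, SD 6; AR1 correlation 0.9; decline 1.00 v 0.75 units per month; the stated death formula; withdrawal 5% per quarter after month 3; first 100 participants at 1:1, the rest at 1:2; two-sided 5% test.

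**Reproducing the plan's own figures.**
- Split: 50 + 159/3 = 103 and 50 + 159 × 2/3 = 156, total 259, as stated.
- Simulated 12-month deaths: 18% and 15%, as stated.
- Simulated power for treatment-by-time in a random-intercept model, with correlation 0.9 between visits: 86.2%, close to the stated 85%. The article states no power for CAFS.

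**Input not in the article.** R2, the share of CAFS rank variance explained by trajectory, is an assumption and is shown over a range. Trajectory is treated as two classes. The minimisation's assignment probability is also assumed (about 0.8).

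**Analytic check.** With trajectory balanced, the true standard error is √(1 − R2) times the one the unadjusted test uses, so

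size = 2 × [1 − Φ(1.96 / √(1 − R2))].

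- R2 = 0: 5.0%.
- R2 = 0.05: 1.96/0.9747 = 2.011, size 4.4%.
- R2 = 0.13: 1.96/0.9327 = 2.101, size 3.6%.

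For power, let s = √(1 − R2) and let θ be the effect in units of the unadjusted standard error. Unadjusted power is Φ((θ − 1.96)/s) and adjusted power is Φ(θ/s − 1.96).

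- R2 = 0.05, θ = 1.96 + 1.036 = 2.996 (nominal 85% power): Φ(1.063) = 85.6% unadjusted, Φ(1.114) = 86.7% adjusted. The gain is about 1 point.
- R2 = 0.13, with unadjusted power set to 78.5% (z = 0.789): θ = 1.96 + 0.789 × 0.9327 = 2.696, and adjusted power is Φ(2.696/0.9327 − 1.96) = Φ(0.931) = 82.4%. The gain is about 4 points.

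**Simulation.** CAFS was scored from all pairwise comparisons under minimisation on site, trajectory and riluzole. The unadjusted rank test was compared with a linear model on the same ranks that included trajectory and riluzole. There were 5,000 null trials and 2,000 trials at 0.25 units per month for each R2.

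| Assumed gap in decline, fast v slow (units/month) | R2 | Size, unadjusted v adjusted | Power, unadjusted v adjusted |
|---|---|---|---|
| 0 | about 0 | 4.7% v 4.9% | 83.0% v 83.3% |
| 0.5 | 0.13 | 3.2% v 4.7% | 78.5% v 83.0% |
| 1.0 | 0.34 | 1.9% v 5.6% | 53.7% v 71.8% |

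A second, separately programmed simulation (1,000 trials per setting) gave 77.9% v 81.8% power at R2 about 0.13, and a gain of about 1 point with strata 0.3 units per month apart (R2 about 0.05). The last row of the table shows how the loss grows; nothing in the article makes so strong a relation likely.

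**Limits.** The tabulated simulation's allocation drifted to about 87:172 rather than 103:156, because it caught up to 1:2 within factor levels. Site and riluzole had no effect on outcome in it. Neither limit changes the direction. The Monte Carlo standard error of the 3.2% size is √(0.0316 × 0.9684/5000) = 0.25 points, so it is compatible with the analytic 3.6%.

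**The case against.** The strongest reply is that the article never says the CAFS test is unadjusted. It names a rank-based test, points to a cited method that is not at hand, and leaves further detail to an SAP that is not shown. Covariates for a secondary rank test are ordinary SAP content. ANCOVA on ranks and a stratified rank test are both rank-based, so either would fit the sentence as written.

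Part of this stands: unadjusted is the natural reading, not a stated choice. But the article is not merely silent. It sets an adjusted default for secondary outcomes, lists CAFS as an exception, and describes an all-against-all comparison ending in mean ranks. An SAP that followed this text would contain an unadjusted test.

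It is also fair to say that the error is on the safe side, that no stated power figure is contradicted, and that R2 is assumed. All of that stands and limits the weight of the point.

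A reader might infer more than the article supports:

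- **That CAFS is a key secondary outcome.** It is listed among the secondary outcomes with no hierarchy.
- **That its confidence interval is wrong.** No CAFS interval is specified; the 95% CI described belongs to the primary area between curves.
- **That the Cox models share the defect.** The Cox wording, "with the exception of time to event outcomes which will be analysed using Cox regression", neither names nor excludes covariates. No Cox model was examined here, so nothing is prescribed for centre frailty or centre strata.
- **That a disagreement between CAFS and the primary result would be only an artefact of adjustment.** The two answer different questions and can differ for other reasons.

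**Conclusion.** The point holds as an inefficiency, not as an invalid test. As described, the CAFS comparison takes no account of a minimised factor that the article itself calls predictive of progression. Type I error is not inflated, and the primary analysis and sample size are untouched.

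The loss is nil if trajectory does not predict the CAFS rank and about 1 point of power at R2 0.05. At R2 0.13 it is about 4 to 5 points, with true size about 3.2% to 3.6%. These figures rest on the Sample size inputs, a two-class trajectory factor and an R2 that the article does not give. The direction does not depend on the exact value of R2; the amount does. The change is worth making because it costs almost nothing.

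**What to change.** In the Secondary outcome section, and in the SAP before unblinding, state one of two analyses for CAFS:

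- ANCOVA on the CAFS ranks with treatment, ALSFRS-R trajectory and riluzole use; or
- a van Elteren-type test stratified by trajectory and riluzole use.

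Include centre only if feasible; the gain shown above does not depend on it, since centre was not in the adjusted model. Report the unadjusted mean rank per arm as description.

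The cost is one sentence of analysis wording. Trajectory and riluzole use are already recorded for randomisation, so no further data or participants are needed. Settling this before unblinding matters, because a choice of adjustment made afterwards could look data-driven.

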### Process evaluation

Alongside the RCT, a mixed-methods process evaluation will be undertaken. This includes qualitative interviews with pwALS, their carers and HCPs to explore context, implementation and mechanisms of impact. Where possible, we will approach patients and carers for separate interviews; however, if preferred, they will be given the choice to interview together, for example, to support with speech difficulties. Analysis of a sample of audio-recorded consultations and HCP intervention visit logs will be used to assess fidelity of intervention delivery. In addition to this, quantitative data will be collected using surveys administered to the intervention arm to investigate the acceptability of the intervention and data analytics on intervention usage.

All interviews will be transcribed verbatim for analysis. Observation notes will be written up after each visit, and reflexive notes will be written up after each qualitative interview to help with data interpretation. The qualitative data will be analysed thematically,^47^ within the broader framework for process evaluations recommended by the Medical Research Council.^48^ To understand the wider implementation issues, the analysis will draw on Normalisation Process Theory^49^ and the Theoretical Framework of Acceptability.^44^ To consider influences on the behaviour of individual pwALS, the COM-B model will be used as an overarching theoretical framework. NVivo software (QSR International) will be used to help structure the analysis.

### Health economics

A cost-utility analysis will be undertaken using the resource use, EQ-5D-3L and mortality data from the trial. The analysis will take an NHS and a broader societal perspective, with an additional analysis that incorporates carer quality-adjusted life years within the incremental cost-effectiveness ratio. This will be supplemented with decision analytic modelling to estimate lifetime cost-effectiveness for the patient cohort recruited to the study.

### Patient and public Involvement

#### Patient and public engagement

Patients and the public have been involved in all aspects of the study. The OptiCALS clinical trial builds on the back of 5 years of work (HighCALS programme) designed to understand the current national service models, the beliefs of stakeholders and the development of behaviour change strategies to support and improve nutritional interventions. The OptiCALS trial has been developed in collaboration with a variety of stakeholders including clinicians, nutritionists, psychologists as well as people living with MND, and their carers. This includes early consultation on study design, outcome measures and recruitment strategies. The OptiCALS Program Steering Committee consists of clinicians, methodologists and PPI members and meets regularly to offer continued input into the conduct, analysis, publication and future work of the study.

## Ethics and dissemination

### Governance

Sheffield Clinical Trials Research Unit on behalf of the sponsor (Sheffield Teaching Hospitals NHS Foundation Trust) coordinates the trial. The chief investigator, project coapplicants, members of the data management team, sponsor, trial manager and other representatives from the Project Management Group, who oversee the operation of the trial and through which amendments will be communicated. The Project Steering Committee (PSC), comprised of clinicians, statisticians, trialists and PPI representatives, provides independent oversight. The independent PSC also undertakes the activities of the Data Monitoring Ethics Committee, providing data monitoring and oversight.

###  Ethical approval

The trial was approved by Greater Manchester—North West Research Ethics Committee, reference 20/NW/0334 on 8 September 2020. The committee will be notified of amendments to the trial as appropriate.

### ISRCTN registration

The program was registered on the ISRCTN registry on 7 December 20 reference: ISRCTN30588041. 20, reference: ISRCTN30588041.

### Dissemination

We will publish the study findings in peer-reviewed academic journals and present at local, national and international conferences where possible. We will publish a short summary of the results on the OptiCALS trial website, accessed by trial participants as well as relevant interest groups.
